##### Retention rates

Retention rate through wave *W*, where *W* = W2 or W3, will be defined as the percentage of consented patients who provide usable data at W1 through wave *W*: (*n*_usable data through wave W_/*n*_consent_) × 100. The lower bound threshold is < 40%. The upper bound threshold is ≥ 60%. The definition of usable data will follow the description previously provided in the *ActiGraph wGT3X-BT* section.

#### Aim 2

Pearson’s correlation coefficient and Bland-Altman analyses will be used to determine if accelerometer-based assessment of physical activity *should* be used within the FFW intervention. Threshold values for the traffic light system for the specific indicators that will be used to evaluate aim 2 are based on inferences drawn from the results of previous research [47, 48].

##### Pearson’s correlation

The linear relationship between the estimates of average minutes per day of MVPA at wave *W*, where *W* = W1 or W2 or W3, produced by the ActiGraph wGT3X-BT, the Fitbit Zip, and the IPAQ, will be estimated with Pearson’s correlation [74]. The lower bound threshold is < .60. The upper bound threshold is ≥ .70.

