### Activity monitors

Wider use of activity monitors (e.g., pedometers and/or accelerometers) to assess physical activity in field-based research on adults began to be steadily advocated for more than a decade ago [19–22]. A primary reason that the use of activity monitors was advocated for was to address long-standing concerns regarding potential limitations for the validity of physical activity estimates based on self-report [23–26]. Accelerometers generally were recommended in field-based research when the indicator of physical activity was to include a dimension of exercise duration and/or intensity (e.g., time spent in moderate to vigorous physical activity (MVPA)) and the cost of the activity monitor was not prohibitive [19–22]. Recent reports suggest that the use of accelerometers to assess physical activity in field-based research on adults may be increasing [27–29]. The scientific importance of this trend is reinforced by troubling findings that suggest only small to moderate relative agreement and large absolute disagreement between estimates of physical activity based on self-report versus accelerometry [30]. Moreover, there is evidence that even some commercial-grade accelerometers that are relatively modest in cost can provide valid estimates of free-living (i.e., occurring outside of controlled laboratory conditions) physical activity among adults [31].

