#### ActiGraph wGT3X-BT

The ActiGraph wGT3X-BT (Pensacola, FL, USA) is a tri-axial research-grade accelerometer that will be used to measure physical activity objectively. ActiGraph devices have been used extensively as a reference (e.g., gold-standard) device to measure free-living physical activity objectively in adults [29]. Monitors will be initialized to collect raw acceleration data at 30 Hz using ActiLife software (version 6.13.3). Upon download, data will be re-integrated to 60-s epochs, and non-wear time will be defined as ≥ 90 continuous minutes of zero counts, with allowance for 2 min of acceleration that are preceded and followed by at least 30 min of continuous zeros [59]. Usable data will be defined as follows: (a) a log sheet with a valid start date is submitted, (b) a monitor is worn for at least 4 days (including one weekend day) with at least 10 h of valid wear time per day, and (c) no evidence of monitor error (e.g., activity counts > 20,000 or lengthy strings of repeated activity counts). Unusable data will be treated as missing data. Average minutes per day of MVPA will be calculated based on established cut points (e.g., > 1952 counts per minute) [60].

The cost of an ActiGraph wGT3X-BT is approximately 225 USA dollars. The ActiGraph wGT3X-BT can store data up to 43 days and sync wirelessly with the ActiLife mobile application; however, the wireless function will be disabled to maximize battery life. A participant will not be able to view any physical activity displays while wearing this device. The pairing of the ActiGraph wGT3X-BT with the Fitbit Zip is based on previous research where at least a moderately high correlation and a moderate level of agreement between measures of average minutes per day of MVPA produced by these two accelerometers has been observed [47, 48].

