### Data analysis

Data analyses will include both quantitative and qualitative approaches. Quantitative analyses will be performed in M*plus* 8.0 under maximum-likelihood estimation with robust standard errors [72]. Missing data will be handled with the default approach under the assumption that data are missing at random [73]. When an estimate of a population parameter (e.g., mean difference) is sought, estimation of a 95% confidence interval (CI) will also be sought. When a qualitative approach is taken (e.g., responses to an open-ended acceptability item; feedback from the center staff), feedback will be summarized based on themes that emerge from the research team’s analysis of the feedback. The particular quantitative and/or qualitative methods that will be used to evaluate each specific aim will vary as a function of the focus of the specific aim.

A traffic light system will be used to evaluate results of specific indicators within each specific aim and with regard to the feasibility of a future definitive RCT [43]. Data observed below a lower threshold (i.e., red light) will indicate a potentially serious problem. Data observed above a lower threshold but below an upper threshold (i.e., yellow light) will indicate that caution is warranted. Data observed above an upper threshold (i.e., green light) will indicate support for the feasibility of a future definitive RCT. The particular threshold values that define the traffic light system will vary by the specific indicator within each specific aim (see Table 2).

**Table 2 Tab2:** Lower and upper bound threshold values that define the traffic light system by aim

Aim	Lower bound threshold	Upper bound threshold
Aim 1		
Acceptability	< 60%	≥ 80%
Recruitment rate	< 40%	≥ 60%
Eligibility rate	< 60%	≥ 80%
Consent rate	< 80%	≥ 90%
Participation rates	< 50%	≥ 70%
Retention rates	< 40%	≥ 60%
Aim 2		
Pearson’s correlation	< .60	≥ .70
Bland-Altman analyses	> 10% of observations beyond M ± 2SD	≤ 5% of observations beyond M ± 2SD
Aim 3		
Acceptability: Quantitative	< 75%	≥ 85%
Acceptability: Qualitative	At least one potentially serious problem	Absence of a potentially serious problem
Aim 4		
Intent to treat	< 0.00	≥ 0.20
Complier average causal effect	< 0.00	≥ 0.20
Indirect effects	Not available	Not available

#### Aim 1

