##### Bland-Altman analyses

Agreement between the estimates of average minutes per day of MVPA at wave *W*, where *W* = W1 or W2 or W3, produced by the ActiGraph wGT3X-BT, the Fitbit Zip, and the IPAQ, will be evaluated with Bland-Altman analyses [75]. First, to test for a systematic difference between pairs of estimates and zero at wave *W*, a paired *t* test will be conducted. Second, to test for proportional bias at wave *W*, a linear regression will be conducted where the difference between pairs of estimates will be regressed on the mean of the two estimates. Third, the Bland-Altman plot will be constructed at wave *W*, where the difference between pairs of estimates is represented on the *y*-axis, the mean of the two estimates is represented on the *x*-axis, and three horizontal lines are depicted with regard to the *y*-axis: *M* + 2SD, *M*, *M* − 2SD. The traffic light system will be based on the Bland-Altman plot and not on a result from a hypothesis test [42–44]. The lower bound threshold is > 10% of observations beyond *M ±* 2SD. The upper bound threshold is ≤ 5% of observations beyond *M ±* 2SD.

#### Aim 3

A descriptive statistic and qualitative data will be used to determine *how* to implement accelerometer-based assessment of physical activity within the FFW intervention.

Threshold values for the traffic light system for the specific indicators that will be used to evaluate aim 3 are based on inferences drawn from the results of previous research [46].

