We are aware of at least four notable strengths for the feasibility study described in this paper. First, the study described in this paper seeks to address a major limitation found in both the 2015 FFW efficacy trial and the 2018 FFW effectiveness trial: measurement of physical activity via self-report only. We believe that providing some initial evidence for the feasibility of including accelerometer-based assessment of physical activity within FFW may be an important next step in the continual development of the intervention, particularly given recent findings that suggest less than high agreement between estimates of physical activity based on self-report versus accelerometer-based [30]. Second, the feasibility study described in this paper attempts to build an evidence-based foundation for a specific response to a global need for readily scalable online behavioral interventions that effectively promote physical activity in adults [16]. We believe that the FFW online behavioral intervention may have the potential to eventually become useful, in some small but important way given the magnitude of the problem, in responding to the global pandemic of physical inactivity [13, 14]. Third, the feasibility study described in this paper attempts to build an evidence-based foundation for a specific response to the troubling global trend toward obesity [1]. We believe that the FFW intervention, because of its conceptual basis in self-efficacy theory, may be effective in promoting physical activity in obese adults [6, 32, 33]. Finally, the feasibility study described in this paper aligns well with recent recommendations put forth by the Community Preventive Services Task Force [33]. More specifically, the feasibility study described in this paper proposes a physical activity intervention for adults with obesity (i.e., FFW) that includes activity monitors (i.e., accelerometers) and promotes physical activity within a more broadly focused weight management program where there is access to a health care provider (i.e., at a local bariatric service center within a major healthcare organization in the Midwest of the USA).

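### The Aim 2 correlation lights (.60/.70) rest on accelerometer-to-accelerometer evidence but also grade the IPAQ pairs, which would probably turn red without that arguing against accelerometry

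*Protocol article*

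**What the plan says.** The Pearson's correlation paragraph under Aim 2 takes MVPA estimates at W1, W2 and W3 "produced by the ActiGraph wGT3X-BT, the Fitbit Zip, and the IPAQ, will be estimated with" Pearson's correlation, and then gives a single rule: "The lower bound threshold is < .60. The upper bound threshold is ≥ .70". Table 2 repeats these values under Aim 2 without naming a pair. The Bland-Altman paragraph handles the same three instruments two at a time ("to test for a systematic difference between pairs of estimates and zero at wave").

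The purpose and source of the rule are also stated:

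- Aim 2 asks whether accelerometer-based assessment should be used within FFW, and Aim 3 assumes a positive answer (Proposed study).
- Under Data analysis, "Data observed below a lower threshold (i.e., red light) will indicate a potentially serious problem".
- At the opening of Aim 2, the thresholds for "the specific indicators that will be used to evaluate aim 2 are based on inferences drawn from the results of previous research", citing references 47 and 48.
- The ActiGraph wGT3X-BT section cites those two references for "at least a moderately high correlation and a moderate level of agreement between measures of average minutes per day of MVPA" from the ActiGraph and the Fitbit Zip.
- For self-report against accelerometry, the Activity monitors section reports "only small to moderate relative agreement and large absolute disagreement between estimates of physical activity based on self-report versus accelerometry".
- The Discussion gives "less than high agreement between estimates of physical activity based on self-report versus accelerometer-based" measurement as a reason why adding accelerometry is an important next step.

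**The concern.** One threshold is asked to serve two different comparisons. Between two accelerometers on the same belt, a correlation under .60 is a plausible warning that the devices do not measure the same thing. Between a questionnaire and an accelerometer, the protocol's own background says that correlations are usually modest, and treats this as motivation for objective measurement. The rule makes no distinction, so an expected and unremarkable IPAQ result would be labelled a potentially serious problem on the question of whether accelerometry should be used.

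Three pairs at three waves give nine correlations, and six of them involve the IPAQ. The document does not say how a red light on an IPAQ pair is to be read. If the investigators set those lights aside once the data are in, they depart from a prespecified rule after seeing the result. If they do not, the answer on which Aim 3 depends is coloured by a threshold that was not derived for that comparison.

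**Working it through.** **No figure to reproduce.** The protocol states no error rate or expected correlation for this rule, and the sample size is set by budget. What can be checked is how the rule behaves.

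**Inputs**

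- Cut-offs: .60 and .70 (Pearson's correlation paragraph; Table 2).
- n = 30: target enrolment (Sample size).
- n = 21 and n = 15: 70% and 50% of 30, the two participation-rate thresholds (Table 2).
- True correlation ρ for an IPAQ–accelerometer pair: not given. I assume .1 to .5 for small to moderate.
- True ρ for ActiGraph–Fitbit: not given. I assume .70 to .80 for moderately high.

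**Formula.** By Fisher's transformation, atanh(r) is approximately normal with mean atanh(ρ) + ρ/(2(n − 1)) and SE 1/√(n − 3). Then P(red) = Φ[(atanh(.60) − mean)/SE] and P(green) = 1 − Φ[(atanh(.70) − mean)/SE], with atanh(.60) = 0.693 and atanh(.70) = 0.867.

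**Worked case, n = 30, ρ = .3.** Mean = 0.3095 + 0.3/58 = 0.3147. SE = 1/√27 = 0.1925. (0.6931 − 0.3147)/0.1925 = 1.97, so P(red) = 0.975.

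**Worked case, n = 15, ρ = .5.** Mean = 0.5493 + 0.5/28 = 0.5672. SE = 1/√12 = 0.2887. (0.6931 − 0.5672)/0.2887 = 0.44, so P(red) = 0.669.

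**IPAQ–accelerometer pair, one wave: P(red) / P(green)**

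| ρ | n = 30 | n = 21 | n = 15 |
|---|---|---|---|
| .1 | 0.999 / 0.000 | 0.994 / 0.001 | 0.979 / 0.004 |
| .3 | 0.975 / 0.002 | 0.945 / 0.010 | 0.902 / 0.029 |
| .4 | 0.914 / 0.012 | 0.865 / 0.033 | 0.812 / 0.068 |
| .5 | 0.759 / 0.054 | 0.711 / 0.097 | 0.669 / 0.149 |

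Bivariate-normal simulation with 100,000 replicates agrees to within about 0.01.

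**ActiGraph–Fitbit pair under the same rule: P(red) / P(green)**

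| ρ | n = 30 | n = 21 | n = 15 |
|---|---|---|---|
| .70 | 0.167 / 0.525 | 0.208 / 0.530 | 0.245 / 0.535 |
| .80 | 0.015 / 0.899 | 0.036 / 0.857 | 0.066 / 0.816 |

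So the light carries information for the device pair. For the IPAQ pairs it mostly returns the result that the background section already leads one to expect.

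**Does the Bland-Altman light share the fault?** That light counts points beyond M ± 2SD of the same differences. Poorer agreement enlarges the SD and moves the limits outward with it. In simulation (200,000 replicates, limits from each sample's own mean and SD, normal differences) more than 10% of points fall outside with probability about 0.1% at n = 30 and 0.2–0.3% at n = 21. With skewed or heavy-tailed differences it stays at or below about 1% at those sizes, and at n = 15 it is roughly 2% to 7%. It does not penalise weak IPAQ agreement.

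**The case against.** The best defence is that some convergence between the IPAQ and an accelerometer is a reasonable thing to want, since the IPAQ was the measure in the 2018 effectiveness trial. A very low correlation could signal trouble on the accelerometer side: usable data need only four days of at least 10 hours, and the belt comes off for water activities. Further, the paragraph does not say in so many words that each pair gets its own light, no rule combines lights into a yes or no, and the authors plainly know that self-report agrees weakly with accelerometry.

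Much of this stands, and it limits the point. A reader might infer that the rule runs backwards for the IPAQ pairs, so that low agreement should count in favour of accelerometry. The documents do not support that, because a low correlation does not show which instrument is at fault. A reader might also infer that six red lights would force a negative answer to Aim 2. No such tally is prescribed. And a reader might extend the criticism to the Bland-Altman light, but that light is largely insensitive to poor agreement, as shown above.

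What the defence does not supply is a basis for .60/.70 on the IPAQ pairs. Wanting some convergence does not justify cut-offs whose cited source is described as a comparison of two accelerometers. Nor does the text restrict the lights: the three instruments are listed together, the threshold follows, and Table 2 adds no qualifier.

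**Conclusion.** The point holds for the correlation light on the IPAQ pairs. The thresholds are ill-matched to those pairs, and red is the probable result: about 67% to 99.9% per pair and wave for an assumed ρ of .1 to .5 and 15 to 30 participants. Green is unlikely but not negligible at the upper end, reaching about 15% at ρ = .5 and n = 15. These figures rest on my reading of small to moderate as .1 to .5 and on approximate bivariate normality; the protocol gives no correlation. That the cut-offs are borrowed from a device-to-device comparison follows from the text alone and does not depend on them.

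This should be fixed, but it is not critical. The lights are advisory, and no participant, allocation or measurement is affected. What is at stake is a clear prespecified reading of Aim 2.

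**What to change.** In the Pearson's correlation paragraph and in Table 2, confine the .60/.70 light to the ActiGraph–Fitbit pair. Report the IPAQ–ActiGraph and IPAQ–Fitbit correlations at each wave with 95% confidence intervals and no light. Add that a low IPAQ correlation does not by itself count against accelerometry. Do not add the converse, that it counts in favour.

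The cost is one sentence restricting the light, one on how the IPAQ correlations are read, and a qualifier in the table. Data collection, sample size and the Bland-Altman analyses are unchanged. The change should be dated before any Aim 2 data are examined.

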##### Bland-Altman analyses

Agreement between the estimates of average minutes per day of MVPA at wave *W*, where *W* = W1 or W2 or W3, produced by the ActiGraph wGT3X-BT, the Fitbit Zip, and the IPAQ, will be evaluated with Bland-Altman analyses [75]. First, to test for a systematic difference between pairs of estimates and zero at wave *W*, a paired *t* test will be conducted. Second, to test for proportional bias at wave *W*, a linear regression will be conducted where the difference between pairs of estimates will be regressed on the mean of the two estimates. Third, the Bland-Altman plot will be constructed at wave *W*, where the difference between pairs of estimates is represented on the *y*-axis, the mean of the two estimates is represented on the *x*-axis, and three horizontal lines are depicted with regard to the *y*-axis: *M* + 2SD, *M*, *M* − 2SD. The traffic light system will be based on the Bland-Altman plot and not on a result from a hypothesis test [42–44]. The lower bound threshold is > 10% of observations beyond *M ±* 2SD. The upper bound threshold is ≤ 5% of observations beyond *M ±* 2SD.

#### Aim 3

A descriptive statistic and qualitative data will be used to determine *how* to implement accelerometer-based assessment of physical activity within the FFW intervention.

Threshold values for the traffic light system for the specific indicators that will be used to evaluate aim 3 are based on inferences drawn from the results of previous research [46].

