### Sample size

Thirty participants will be targeted for enrollment in this study. There are three rationales for the target sample size. First, the target sample size fits well within the range of sample sizes often observed in pilot and feasibility trials [45]. Second, and with regard to aim 1 through aim 3 of this study, the target sample size is consistent with sample sizes observed in similar research [31, 46–48]. Third, and with regard to Aim 4 of this study, the target sample size is based on budgetary constraints and not a sample size determination for a desired level of statistical power [42–44]. Budgetary constraints preclude enrollment of more than 30 participants in this study.

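### The Aim 2 Bland-Altman light counts points outside limits computed from those same points, so it cannot register how well the methods agree

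*Protocol article*

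**What the plan says.** The Protocol article (Data analysis, Aim 2) names two indicators for deciding whether accelerometry should be used: "Pearson’s correlation coefficient and Bland-Altman analyses will be used to determine if accelerometer-based assessment of physical activity" should be adopted within the intervention. For the second, the Bland-Altman analyses section describes three steps at each wave for each pair among the ActiGraph, the Fitbit Zip and the IPAQ:

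- a paired t test for systematic difference;
- a regression of the difference on the mean, for proportional bias;
- a plot "where the difference between pairs of estimates is represented on the" vertical axis, with horizontal lines at M + 2SD, M and M − 2SD.

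It then states: "The traffic light system will be based on the Bland-Altman plot and not on a result from a hypothesis test". Table 2 gives the cut-offs: red is "> 10% of observations beyond M ± 2SD" and green is "≤ 5% of observations beyond M ± 2SD". On their origin the protocol says: "Threshold values for the traffic light system for the specific indicators that will be used to evaluate aim 2 are based on inferences drawn" from earlier studies. It gives no acceptable bias or acceptable width of the limits in minutes per day.

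**The concern.** A Bland-Altman analysis reports two things: the mean difference between methods, and how wide the limits around it are. Whether these are tolerable has to be judged against an outside standard. The rule here compares the differences only with their own mean and their own spread. Two devices that differ by an hour a day, and two that agree to the minute, face the same chances of green, yellow and red if their differences have the same distributional shape.

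At stake is the meaning of one of the two lights that answer Aim 2 and inform a definitive trial. The other light, Pearson's correlation, responds to scatter but not to a constant offset. Neither Aim 2 light can therefore register a constant offset.

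**Working it through.** The protocol gives no operating characteristics for this light, so there is no figure of its own to reproduce.

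**Inputs**

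- Lines and cut-offs: Bland-Altman analyses section and Table 2. M and SD are read as those of the differences plotted at that wave. This is the natural reading, since no other source for them is given.
- Largest n per plot: 30 (Sample size: "Thirty participants will be targeted for enrollment in this study").
- Plausible n per wave: the participation thresholds of 50% and 70% give 0.50 × 30 = 15 and 0.70 × 30 = 21.

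**Step 1: bias and scale cancel.** A difference d is counted when |d − M| > 2SD. Replace every d by a + b·d with b > 0. Then M becomes a + b·M and SD becomes b·SD, so the condition is |b(d − M)| > 2b·SD. This is the same condition, and the count is unchanged for every a and b. In simulation with the same normal draws at n = 30, bias/SD of 0/1, 0/60, 30/60 and 100/200 min/day all gave 67.8% green, 32.1% yellow and 0.1% red.

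**Step 2: the count is bounded.** Each counted point adds more than 4SD² to a sum of squares equal to (n − 1)SD². So k < (n − 1)/4. At n = 30 this is 29/4 = 7.25, so at most 7 points (23%) can lie outside, however bad the agreement.

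**Step 3: rounding of counts.**

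| n | 1 point | 2 points | 3 points | Green needs | Red needs |
|---|---|---|---|---|---|
| 15 | 6.7% | 13.3% | 20.0% | 0 | 2 or more |
| 19 | 5.3% | 10.5% | 15.8% | 0 | 2 or more |
| 20 | 5.0% | 10.0% | 15.0% | 0 or 1 | 3 or more |
| 21 | 4.8% | 9.5% | 14.3% | 0 or 1 | 3 or more |
| 29 | 3.4% | 6.9% | 10.3% | 0 or 1 | 3 or more |
| 30 | 3.3% | 6.7% | 10.0% | 0 or 1 | 4 or more |

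**Step 4: chance of each light.** Simulation with 200,000 datasets per cell, SD with divisor n − 1:

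| n | Normal: green/yellow/red | Red, t with 3 df | Red, lognormal |
|---|---|---|---|
| 15 | 54/44/2.4% | 6.7% | 6.5% |
| 18 | 43/51/6.1% | 15% | 16% |
| 19 | 40/52/7.7% | 19% | 20% |
| 20 | 90/9/0.1% | 0.6% | 0.3% |
| 21 | 89/11/0.3% | 1.0% | 0.6% |
| 29 | 70/27/3.3% | 9.5% | 8.0% |
| 30 | 68/32/0.1% | 0.5% | 0.3% |

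The average share outside over these n is about 3 to 4% for normal differences and 5 to 6% for the other two shapes. Going from 20 to 19 usable participants drops green from 90% to 40% for normal differences, with no change in agreement.

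**Step 5: good and bad agreement compared.** At n = 30, two nearly equivalent methods (r about .95) gave 68% green and 0.1% red. Two unrelated methods with a 40 min/day bias gave 67% green and 0.1% red.

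**Step 6: contrast with a fixed limit.** For zero bias and normal differences, the share outside ±L is 2(1 − Φ(L/SD)): 0.09% at SD = 0.3L, 4.6% at 0.5L, 32% at L and 62% at 2L. A limit set from outside the data moves with agreement.

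**The case against.** **Bias would not go unreported.** The paired t test, the proportional-bias regression and the plotted mean are all planned, and the Data analysis section seeks a 95% confidence interval for estimates such as a mean difference. An hour-a-day offset would be visible in the output. This stands, and it limits the harm to the light itself. It does not rescue the light, because the protocol expressly keeps the tests out of it.

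**A reader might infer that red will almost never appear.** The documents do not support that. It holds at n = 20, 21 and 30, but these are low points of a sawtooth. The participation thresholds allow n = 15 to 19, where red runs from 2 to 8% per plot for normal differences and about 6 to 20% for the other two shapes. Three pairs at three waves give nine plots. If these were independent (an assumption), at n = 18 with normal differences the chance of at least one red is 1 − (1 − 0.061)^9 = 43%. The supportable statement is that red does not track agreement.

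**The thresholds come from earlier studies, and this is a small pilot.** Those studies are not available here, but no source can alter the cancellation in Step 1. The pilot setting does bear on severity: the lights signal a serious problem, caution or support, no binding stop rule is attached, and the underlying estimates are unaffected.

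**The count can flag outliers.** True, and useful as a data check, but that is not agreement.

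**Conclusion.** The rule is wrong as written. The share of differences beyond M ± 2SD does not change with constant bias or with the width of the limits, so the light carries no information on either. That result is exact and needs only the reading that M and SD come from the plotted differences.

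The probabilities rest on assumed shapes (normal, t with 3 df, lognormal) and on n between 15 and 30. Red is about 1% or less at n = 20, 21 and 30 under all three shapes, and reaches about 8% (normal) or 20% (lognormal) at n = 19. Wherever red or yellow occurs, it reflects shape and rounding.

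This should be fixed, but it is not critical: the planned outputs still allow agreement to be judged, and no confirmatory inference depends on this light.

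**What to change.** Delete the rule on the share of observations beyond M ± 2SD from the Bland-Altman analyses section and from Table 2. Before data are seen, state a maximum acceptable difference δ in min/day for the ActiGraph-Fitbit pair, with the team's own justification. Then set the light as follows:

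- green: both limits of agreement lie within ±δ;
- yellow: the mean bias lies within ±δ but at least one limit does not;
- red: the mean bias lies outside ±δ.

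Report 95% confidence intervals for the bias and for both limits, since 15 to 30 participants estimate them imprecisely.

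Report the IPAQ pairs descriptively, or give them their own δ. The Activity monitors section and the first strength in the Discussion treat disagreement between self-report and accelerometry as already documented and as a reason for this study. A single δ for all pairs would count that disagreement against accelerometry. The 21.36 min/day figure in the physical activity monitoring section should not serve as δ by default: it is a participant feedback category, not an agreement margin.

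The plot, the paired t test and the regression stay as planned. The cost is committing to a δ and rewording one paragraph and two table cells. No new data are needed.
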